## Abstract

**Background:**

The limited or uncertain access to adequate food in elderly people includes not only economic restrictions but also inability of food utilization due to functional or cognitive impairment, health problems, and illiteracy.

**Objective:**

The aim of this work is to present the protocol of the randomized controlled trial Saúde.Come Senior, an educational and motivational television (TV)-based intervention to promote healthy lifestyles and decrease food insecurity in elderly people.

**Methods:**

A randomized controlled study will be conducted in subjects aged 60 years and older with food insecurity, identified at 17 primary care centers in the Lisboa e Vale do Tejo health region in Lisbon, Portugal. The primary outcome will be the changes in participants’ food insecurity score (evaluated by the Household Food Insecurity Scale) at 3 months. Change in other outcomes will be assessed (dietary habits, nutritional status, physical activity, health status, and clinical outcomes). Subjects will be followed over 6 months; the intervention will last 3 months. Data collection will be performed at 3 different time points (baseline, end of intervention at 3 months, and follow-up at 6 months). The intervention is based on an interactive TV app with an educational and motivational program specifically developed for the elderly that has weekly themes and includes daily content in video format: (1) nutrition and diet tips for healthy eating, (2) healthy, easy to cook and low-cost recipes, and (3) physical exercise programs. Furthermore, brief reminders on health behaviors will also be broadcasted through the TV app. The total duration of the study will be 6 months. The intervention is considered to be effective and meaningful if 50% of the individuals in the experimental group have a decrease of 1 point in the food insecurity score, all the remaining being unchanged. We expect to include and randomize 282 (141 experimental and 141 control) elderly with food insecurity. We will recruit a total of 1,128 subjects considering that 50% of the target individuals are food insecure (based on INFOFAMÍLIA Survey) (567) and about 50% of those will adhere to the study (282).

**Results:**

The randomized controlled trial with the 12-week home-based intervention with a comprehensive program on healthy eating and physical activity delivery is planned to start recruiting participants at the end of 2017.

**Conclusions:**

This study will assess the efficacy of this innovative tool (Saúde.Come Senior) for disseminating relevant health information, modifying behaviors, and decreasing food insecurity in an easy, low-cost, and massive way.

## Introduction

The world is facing a situation without precedent: soon there will be more older people than children and more people at extreme old ages than ever before [1]. In fact, by 2025 more than 20% of Europeans will be aged 65 years or over, with a particularly rapid increase in the number of over 80s [1]. Portugal has a high proportion of elderly persons and is one of the European countries with the lowest birth rate [2]. As both the proportion of older people and the length of life increase throughout the world, some key questions arise. Will population aging be accompanied by a longer period of good health, a sustained sense of well-being, and extended periods of social engagement and productivity, or will it be associated with more illness, disability, and dependency? What are the consequences of the European economic distress on the health of the elderly?

The impact of an economic crisis may be particularly acute for older people, mainly for those who are physically vulnerable, living in poverty, or dependent on private pensions, leading to adverse lifestyles and health outcomes. Adverse lifestyles and health outcomes include increasing food insecurity; use of tobacco, alcohol, and drugs; increasing depression and anxiety; and a general neglect of overall health [3]. In fact, elderly people with food insecurity report reduced quality, variety, or desirability of diet which leads to higher morbidity through decompensated chronic noncommunicable diseases (diabetes mellitus, hypertension, dyslipidemia), low muscle strength with less mobility, higher mortality, and higher health care costs [4,5]. Many have significant cognitive, psychiatric, and physical problems yet do not seek assistance. Assessment and intervention in these cases requires an interdisciplinary approach. An understanding of risk factors, the clinical evaluation process, competency issues, and basic management strategies is integral to good care.

According to the internationally recognized definition, “food security is the situation that exists when all people, at all times, have physical and economic access to sufficient safe and nutritious food that meets their dietary needs and food preferences for an active and healthy life” [6]. In contrast, food insecurity is a broad concept that includes attributes related with the uncertainty or worry about food, inadequate quality of food, inadequate quantity of food, food acquired through socially unacceptable means, and lack of consistent access to adequate food [7]. Food insecurity is often associated with economic constraints. The rates of food insecurity have been rising worldwide [7]. While the United States is one of the wealthiest nations in the world with a rich and abundant supply of food and resources, 14.3% of US households were food insecure at some point during 2013 [8]. A study of Portuguese primary care center attendees in 2013 showed that 50.7% were food insecure [9]. Furthermore, more than one-third of Portuguese adults with food insecurity are overweight (41.0% in moderate food insecurity and 37.7% in severe food insecurity categories) [10]. This situation needs particular attention if we consider that Portugal is one of the Organization for Economic Cooperation and Development countries with highest levels of income inequalities [11].

Food insecurity has been shown to be associated with poor self-rated health and several noncommunicable diseases such as diabetes, hypertension, fibromyalgia, and osteoporosis [12,13].

In general, food insecurity has been less well studied in the elderly. Data from the United States suggested that food insecurity decreases as age increases. The prevalence of food insecurity was 20.4% among US adults aged between 40 to 49 years and 15.7% among older adults aged between 60 to 69 years [14]. The same trend was observed for Canada: the prevalence of food insecurity was lower in elderly people (16% vs 29% for the total sample) [15]. However, the nutrition and health consequences might be potentially more severe for older adults. In elderly populations, food insecurity might occur as a result of other factors rather than constraints of financial resources. There is evidence that food insecurity among the elderly can be associated with health or mobility problems (functional impairment), which can also compromise the access to healthy food.

Indeed, the concept of food insecurity in elderly persons also includes nutritional deficits and other relevant aspects related with limited or inability to use food due to functional impairments and health problems [16,17]. For older adults, who generally require special attention for optimal nutrition, food insecurity has been a risk factor for poor nutritional status and low muscle power especially in those with physical disabilities, increasing hospitalizations and death [4,5].

Information and communication technology (ICT) solutions can be used as a personalized cost-effective smart model of health empowering subjects to take more responsibility for their own health and quality of life. Moreover, ICTs have the potential to make a major contribution to improve access to quality services while controlling costs. Elderly people spend a significant amount of time watching television (TV) [18], which can be used as a tool to improve health literacy and a vehicle for promoting health lifestyles. Promoting healthy lifestyles in elderly populations is crucial to slow physical decline and improve well-being, delay the deterioration of health, and reduce the risk of mortality [19].

For this study, we hypothesized that a home-based intervention program on dietary and physical activity through a TV app will improve food security as well as clinical endpoints such as nutritional status, body composition, balance, strength, and quality of life in the elderly population. Considering the broad definition of the food insecurity concept and its 4 main dimensions (availability of food, physical and economic access to food, food utilization, and stability of the other dimensions) [20], our intervention program will be focused on the dimension of food security related to the use or utilization of food, which might be affected by literacy in food and health. Our hypothesis is that a TV-based intervention might have a large potential in promoting healthy lifestyles among low socioeconomic status groups and for people with low literacy, since TV is the most frequently used ICT by low literacy people.

This paper describes the study protocol of a home-based randomized controlled trial aimed at evaluating the impact of a TV-based intervention on healthy lifestyle promotion in elderly subjects in food insecurity reduction.

## Methods

### Design Overview

This is a randomized controlled study based on an intervention program on diet and physical activity that uses a TV app in about 282 elderly subjects aged 60 years and older with food insecurity identified at 17 primary care centers in the *Lisboa e Vale do Tejo* health region in Portugal. Subjects will be followed over 6 months after the beginning of intervention, which will last 3 months. The research protocol of this study is illustrated in the study design flowchart depicted in Figure 1.

**Figure 1 figure1:**
[figure not shown]
Study design flowchart.

### Study Population and Recruitment Plan

A convenience sample of food-insecure elderly people from 17 primary care centers of *Lisboa e Vale do Tejo* health region will be enrolled in this study. All elderly subjects who attend health services in the selected primary care centers during the recruitment period will be approached by our research team and asked to complete a questionnaire for the initial screening. The questionnaire includes a food insecurity scale to identify food-insecure elderly persons, and an authorization request form will be provided to obtain consent for a further contact. All elderly subjects identified as food insecure will be invited to participate in this study. The baseline assessment will be performed during an appointment at the primary care center with a multidisciplinary team that includes a medical doctor, nurse, nutritionist, and physiotherapist. The medical doctor will ask for informed consent and check inclusion and exclusion criteria.

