### Eligibility

To be eligible for this randomized controlled study, subjects must fulfill all of the following inclusion criteria: (1) aged 60 years or older, (2) identified as food insecure in the recruitment [21], (3) able and willing to give written informed consent and phone number contact and comply with other requirements of the study protocol, (4) Portuguese speaker or able to understand Portuguese, (5) noninstitutionalized and living in a private household in Portugal, (6) have electricity at home, and (7) have cable TV with box at home. The exclusion criteria are as follows: (1) inability to comply with study protocol (hearing/visual loss, cognitive impairment, etc); (2) absolute contraindication to exercise; (3) have cable TV operated by other companies than MEO, Vodafone, or NOS; and (4) have a household member involved in this study.

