A nutrition and physiotherapy assessment will be performed at baseline and end of intervention assessment (at 3 months). The nutritionist will collect data regarding food insecurity (Household Food Insecurity Scale [HFIS] adapted from the US Department of Agriculture Household Food Security Survey Module [21]), dietary habits (2-day 24-hour diet recall, Prevención con Dieta Mediterránea [PREDIMED] index [31], and food frequency questions), anthropometric data (height, weight, and waist circumference), body composition data obtained by bioimpedance (fat mass, fat-free mass, total body water), attitudes and barriers on diet, food expenses, and other resources for food. Regarding the dietary habits assessment, a second 24-hour diet recall will be performed by phone call interview performed within 1 week.

Physiotherapy assessment will be conducted aiming at collect data regarding physical activity (Elderly Mobility Scale [EMS] [32] and International Physical Activity Questionnaire [IPAQ]) and muscle strength (hand grip, knee extension, and hip flexion by using a dynamometer). The assessment scales used in the study are all Portuguese-validated versions, and the average time for the evaluation will be 90 minutes.

The nurse will perform a structured questionnaire in order to capture baseline knowledge on healthy lifestyles. This questionnaire will be repeated during the 3-month and 6-month follow-up assessments.

Blood samples will also be collected in order to obtain data regarding the nutritional status and serological biomarkers of cardiovascular risk (albumin and prealbumin levels, insulin resistance, cholesterol levels, hemoglobin A_1c_, adipocytokines, high sensitivity C-reactive protein, interleukin 1, interleukin 6, and tumor necrosis factor).

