### Outcome Measures

The primary outcome assessed will be the changes in participant food insecurity score (evaluated by the HFIS) from baseline to 3 months. Secondary outcomes at 3 months will be changes in dietary habits (evaluated by 2-day 24-hour recall, PREDIMED index [31], and food frequency questions), changes in indicators of nutritional status (body mass index [BMI] and albumin and prealbumin levels), changes in muscle strength improvement (evaluated by dynamometer), changes in quality of life (EQ-5D-3L) [33], changes in fatigue scale (FACIT-F) [34], changes in serological markers of cardiovascular risk (insulin resistance, cholesterol levels, hemoglobin A_1c_, high sensitivity C-reactive protein, adipocytokines, interleukin 1, interleukin 6, and tumor necrosis factor), changes in physical activity (EMS [32] and IPAQ [35]); changes in body composition balance evaluated by bioimpedance, changes in inpatient admissions and outpatient appointments, changes in falls, and changes in knowledge regarding healthy lifestyle.

The secondary outcomes at 6 months will be changes in participant food insecurity score, changes in dietary habits (2-day 24-hour recall, PREDIMED index [31], and food frequency questions), changes in quality of life (EQ-5D-3L) [33], changes in fatigue scale (FACIT-F), changes in physical activity (IPAQ) [35], changes in inpatient admissions and outpatient appointments, changes in falls, and changes in knowledge regarding healthy lifestyle.

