### Data Analysis

Analysis will be performed with Stata software (StataCorp LLC). Continuous variables will be reported as mean and standard deviation (or in case of nonnormal distribution as median and interquartile range). Categorical variables will be displayed as frequencies or proportions. The association between food security status, dietary data, and health outcomes will be assessed through chi-square analysis of baseline data.

To assess the effect of the interventional program on food security, dietary intake, nutritional status and body composition, quality of life, muscle strength, fatigue scale, physical activity habits, and serological markers of cardiovascular risk, 2-tailed *t* tests will be used to compare the amount of change within each group (baseline, end of study [at 3 months] and follow-up [at 6 months]). Independent sample *t* tests will be used to compare the intervention group and control group on the same outcomes.

Dietary intake assessed with 2-day 24-hour recall will be analyzed according to the recommended number of servings from each food group of the Portuguese Food Wheel [37]. Intakes of micronutrients that tend to be low in vulnerable population groups (iron, calcium, folate, and vitamins A, C, and D) will be also analyzed. The percentage of individuals meeting the Estimated Average Requirement or Adequate Intake for iron, calcium, folate, and vitamins A, C, and D will be calculated [38]. Food Processor Nutrition Analysis software (ESHA Research) will be used to estimate the intakes of energy, macro-, and micronutrients.

The association between each outcome and the candidate covariables will be performed using generalized models. We will use multivariate logistic and linear (according to the outcome) regression models. The candidate covariates will be first analyzed by univariate regression. Covariates will enter the multivariate models if their *P* value is less than .25 in univariate analysis or considered clinically relevant in this setting. The selection of covariates will be stepwise by backward selection, according to the level of significance (<.05). Multilevel analysis and sensitive analysis will be performed when appropriate.

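### The screening food-insecurity score looks usable as a second pre-treatment reading, but the primary t test on change leaves it out; adding it as a covariate is a cheap precision gain of uncertain size

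*Protocol article*

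**What the plan says.** Study Population and Recruitment Plan describes the screening step: "The questionnaire includes a food insecurity scale to identify food-insecure elderly persons". Eligibility makes the result a condition of entry: "identified as food insecure in the recruitment [21". The bracketed reference is the one that Data Collection gives for the HFIS.

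Data Collection then describes a second reading: "The nutritionist will collect data regarding food insecurity (Household Food Insecurity Scale [HFIS] adapted from the US Department of Agriculture Household Food Security Survey Module". On timing it says: "A nutrition and physiotherapy assessment will be performed at baseline and end of intervention assessment (at 3 months".

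Outcome Measures defines the primary outcome as "changes in participant food insecurity score (evaluated by the HFIS) from baseline to 3 months". Sample Size rests on an independent-samples t test of mean change, and Data Analysis confirms that such "tests will be used to compare the intervention group and control group on the same outcomes". The regression models later in Data Analysis choose their covariates by significance or clinical relevance ("Covariates will enter the multivariate models if their" univariate P value is below .25, followed by backward selection). They name neither food-insecurity score.

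Randomization, Allocation, and Blinding stratifies by gender and food-insecurity level (low/moderate versus severe), without saying whether the level comes from the screening or the baseline reading.

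**The concern.** A single reading of a household score is a noisy measure of its usual level. If the screening scale is the HFIS, the trial will hold a second reading taken before treatment. The stated primary analysis uses it only as a gate and perhaps to form a stratum. A pre-randomisation covariate that predicts the 3-month score narrows the confidence interval for the treatment effect without extra patients or visits. The target of 141 per arm sits at 80% power with no margin, so precision already paid for is worth having. What is at stake is efficiency, not the validity of the comparison.

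**Working it through.** **1. The plan's own figure.** Inputs from Sample Size: difference 0.5, SD of change 1.5, alpha .05, power 0.80. For a two-sided test, n per arm = 2(1.960 + 0.842)² × 1.5²/0.5² = 2 × 7.849 × 9 = 141.3. The stated 141 is reproduced (142 if rounded up; 142.2 from the t distribution). A one-sided test would need 112. Power at 141 per arm is 79.9% (normal) or 79.7% (t).

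**2. Stable underlying level, no selection.** Let screening, baseline and 3-month scores share one variance s² and one correlation ρ. The documents give no ρ, so it is varied. Holding the variance of change at 1.5² = 2.25 gives s² = 2.25/[2(1 − ρ)]. Residual variances are:

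- baseline HFIS as covariate: s²(1 − ρ²)
- baseline and screening as covariates: s²[1 − 2ρ²/(1 + ρ)]
- ratio of the second to the first: (1 + 2ρ)/(1 + ρ)²

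At ρ = 0.5: s² = 2.25, and the two variances are 1.688 and 1.500, a ratio of 2/2.25 = 0.889.

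| ρ | Variance, baseline only | Variance, both | Further cut | n per arm for 80% | Power at 141 |
|---|---|---|---|---|---|
| 0.3 | 1.463 | 1.385 | 5% | 92 → 87 | 93.5% → 94.6% |
| 0.5 | 1.688 | 1.500 | 11% | 106 → 95 | 89.8% → 92.9% |
| 0.7 | 1.912 | 1.588 | 17% | 121 → 100 | 85.9% → 91.5% |
| 0.8 | 2.025 | 1.625 | 20% | 128 → 103 | 83.9% → 90.9% |

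**3. Stable level, participants selected on screening.** Sample Size assumes that 50% of those screened are food insecure. Keeping the upper half of the screening score (normal scores, ρ before selection) narrows its spread and its value as a predictor.

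| ρ | Cut from baseline adjustment, against the t test | Further cut from screening | n per arm | Power at 141 |
|---|---|---|---|---|
| 0.3 | 37% | 2% | 89 → 87 | 94.2% → 94.6% |
| 0.5 | 30% | 5% | 100 → 95 | 91.6% → 92.9% |
| 0.7 | 22% | 10% | 111 → 100 | 88.6% → 91.5% |
| 0.8 | 17% | 13% | 118 → 102 | 86.7% → 91.0% |

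**4. Correlation that fades with time.** Let r_sb, r_b3 and r_s3 be the screening-baseline, baseline-3-month and screening-3-month correlations. The further cut is (r_s3 − r_sb·r_b3)²/[(1 − r_sb²)(1 − r_b3²)].

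- 0.8, 0.7, 0.65: (0.65 − 0.56)²/(0.36 × 0.51) = 0.0081/0.1836 = 4.4%.
- 0.8, 0.6, 0.55: 0.07²/(0.36 × 0.64) = 0.0049/0.2304 = 2.1%.
- 0.8, 0.6, 0.48: the numerator is zero, so the cut is 0%.

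**5. A score shaped more like the real one.** Simulation of a skewed 0-14 integer score, keeping people who score at least 1 at screening, with single-reading reliability 0.5-0.9 (all assumptions):

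- Underlying level constant: further cut about 5-22%, toward the lower part if the stratum is formed from the screening score.
- Mild drift: about 3-10%. Stronger drift: about 1-6%. With underlying correlations of 0.9 from screening to baseline and 0.8 from baseline to 3 months, 0.7-4%.

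**6. In participants.** A cut c is worth 282/(1 − c) − 282 extra participants: about 3 at 1%, 15 at 5%, 31 at 10% and 70 at 20%. The interval shrinks by 1 − √(1 − c): about 5% at a 10% cut and 11% at a 20% cut.

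**The case against.** Change from the trial baseline is ordinary practice, and a second pre-treatment covariate is something a separate analysis plan could add. Data Analysis also admits covariates judged clinically relevant. This stands as far as it goes: the point is a refinement, and nothing here is stated wrongly. But the article does fix the primary test and sizes the trial on it, and data-driven covariate selection does not secure either score a place in the primary comparison.

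The second objection is about size. The planned test is not baseline-adjusted, and most of the dependable gain comes from that first step. With selection allowed for and ρ = 0.5, baseline adjustment takes power from 79.9% to 91.6%, and the screening score adds only 1.3 percentage points. This stands too.

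A reader might infer a sure saving worth dozens of participants. The documents do not support that: the upper figures require that a household's true level does not change from screening to 3 months, and no correlation is given. A reader might also infer that selection on the screening score biases the planned test through regression to the mean. It does not, since randomisation leaves that effect equal in expectation in both arms.

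Three facts are inferences. The recruitment section says only that a food-insecurity scale is used; its identity with the HFIS rests on the shared reference. The order of baseline HFIS and randomisation is not spelled out, though consent and eligibility are checked at the baseline appointment and the strata need a food-insecurity level. Finally, being identified as food insecure does not guarantee a complete numeric score that can be linked.

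**Conclusion.** The point holds as a cheap precision gain. Each randomised participant appears to have two pre-treatment readings, and the stated primary comparison uses one. Beyond baseline adjustment, the screening score would lower residual variance by roughly 5-20% if the underlying level is stable (down to 2% with selection and a correlation of only 0.3), by about 1-10% if it drifts, and possibly by almost nothing. The t test as planned is valid. The range rests on assumed correlations and reliabilities, and on the screening scale being the HFIS with baseline HFIS taken before allocation.

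**What to change.** - Link the numeric screening score to the trial record, and have the baseline consent cover its use, because the screening-stage authorisation is described only as permission for further contact.
- Prespecify the primary between-arm comparison of 3-month HFIS as a linear model with treatment, baseline HFIS, the stratification factors and the screening score as a further continuous covariate. The time point and the scale stay as they are.
- Do not average the two scores into one baseline. Participants are selected on the screening score, and as a separate term the model sets its weight.
- State that the screening scale is the HFIS (if it is), that baseline HFIS precedes allocation, and which reading defines the stratum.

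The cost is one linked variable, one model term (one degree of freedom among 282 participants) and one consent line. No visit, procedure or participant is added. It is best settled before recruitment, which Results describes as still planned.
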